## 5.9 Economic evaluation

The economic evaluation will be conducted. We will consider costs from the perspective of health services instead of the societal perspective because the aim of the study focuses on how SINEMA model could solve healthcare related issues and stroke survivors are already being in the community with very few of them have official and stable work poststroke. Thus, pension costs and worker productivity are not as relevant to our study design. Data on costs of the intervention such as study design, APP development and incentives for the village doctors, will be collected from project financial reports. Data on the cost related to utilization of health care

services and medications will be collected at the 1-year follow-up surveys. This information will be supplemented by insurance claims data focusing on both inpatient and outpatient costs. For the trial-based evaluation, cost effectiveness will mainly be assessed using 2 indicators: cost per unit reduction in systolic blood pressure and cost per unit increase in quality adjusted life year (QALY). If suitable, we will conduct analysis for long-term cost-effectiveness by considering the situation beyond the trial, a decision-analytic model will be developed to enable long-term outcomes to be simulated, which will draw on the literature and available databases. Sensitive analysis will be conducted to determine the robustness of the estimates.

## **6. DATA MANAGEMENT PLAN**

### **6.1 Data description**

The following database will be generated and managed by the research team with supervision from the international steering committee.

#### *Data from patients' screening*

During the patients' screening, village doctors will collect basic information about all stroke patients in their village. Data includes name, gender, age, phone number and stroke history. These information will be mainly used for patients' recruitment and no information will be used for data analysis.

#### *Intervention-related data*

Intervention related data will be collected through SINEMA APP by Village doctors and VPs. During each patients' follow-up, Village doctors will collect data about patients' blood pressure, recent hospital visits, and medication use. VPs will collect data about patients' Barthel Index and physical activity. These information will be used mainly for project management and process evaluation. Some data could be used as a supplementary database for the evaluation.

#### *Data for outcome evaluation*

Evaluation-related data includes assessments of patients on the primary and secondary outcomes of the trial, including systolic blood pressure, stroke occurrence, disability and dependence, medication adherence, health status, activities of daily living, mobility, and risky lifestyles.

#### *Data for process evaluation*

Data collected from the process evaluation are audio recordings of the interviews and focus group analysis conducted with the patients, their caregivers, village doctors and health promoters. The topics of these interviews include the effectiveness of the intervention, and feedback and comments on the intervention and the use of the SINEMA APP.

#### *Data for economic evaluation*

Before the baseline data collection, personal ID number and social security number will be collected by project manager or county manager to support the economic evaluation. Data for the economic evaluation includes costs of the intervention, and patients' medical cost and quality of life. This information will be supplemented by insurance claims data.

904

## 905 6.2 Format and data standards

906 Data will be collected and stored in formats generally accepted within the public health  
907 community. Intervention related data will be collected through the App and download from the  
908 server for analysis. Evaluation data will be collected through *Qualtrics*, an electronic data  
909 collection system. Qualitative data will be captured in MPEG-1 Audio Layer 3 (.mp3) format.  
910 Individual interviews and focus group interviews will be transcribed into text files using *MS Word*  
911 (docx, or .doc). This qualitative data, interview transcripts, and any field notes will be imported  
912 into and analyzed using *QSR Nvivo*.

913

## 914 6.3 Data storage, security and backup

915 All data associated with this project will be maintained in strict compliance with both  
916 international and local policies. All associated digital research data will be physically stored on  
917 an encrypted secure server maintained by the research team using standard file formats. No  
918 data will reside on portable or laptop devices. The digital files with identifiers and recordings will  
919 be stored on a password-protected hard drive that has been encrypted. Paper files and the  
920 password-protected hard drive will be kept in a locked storage cabinet and the key protected by  
921 the P.I., only giving authorized personnel access to the key.

922 The researchers in Duke Kunshan University are responsible for storage, maintenance and  
923 back-up of the data based on the data security level. Network-stored research data is backed  
924 up on a daily basis to a separate password-protected secure server maintained by Duke  
925 Kunshan University.

### 926 *Data management, curation and storage*

927 Approaches include: (i) curation in SAS following a normalized relational database design; (ii)  
928 labelling, formatting, documenting, and deriving variables in a consistent manner over time and  
929 across samples; (iii) an established file management strategy (folder structure and file naming);  
930 (iv) secure storage, backup and access to the IT department of the Institute; (v) multiple layers  
931 redundancy, eg: raw data will be stored in duplicate on password-protected external hard drives  
932 kept in separate secure locations; and (vi) use of flexible formats to facilitate analyses in  
933 statistics packages.

### 934 *Storage of personal data*

935 Personal identifiable data (including name, ID and phone number of the participants) will only be  
936 used when essential for generating list of participants for follow-up, matching with the health  
937 information system and for supporting message dispatching as part of the intervention. This  
938 information will be stored separately from other collected data and only accessed by the study  
939 PI.

940 To protect the privacy and confidentiality of the identifiable information, we will separate the data  
941 collection of identifiable information from other data. After the data are collected, entered and  
942 digitized, all personal identifiable information including the ID will be removed from the final data  
943 file for data analysis. All devices used to access and process data include password-protected

desktop computers. Data are stored on the secure institutional server protected by firewalls. No remote access is employed.

In addition, no personal data will be linked with the response at any time during the study. The data analysis and report writing will be conducted based on an aggregated format.

## 6.4 Access, sharing and dissemination

The P.I. will be responsible for ensuring that all project members are aware as to the ownership of data and who may access them and under what conditions. Online access to the data will be password protected. All research groups have been trained in human subject protection and only trained project staff operating under the IRB approval for the project will have access to the confidential individually identifiable data. After the data are collected, entered, and digitized, the identifiable information will be stored in a separate dataset that will be password protected. All data will be aggregated or de-identified for publication and baseline and follow-up surveys will be linked by study ID only. Paper files will be kept in a locked cabinet and access to the key will be limited to the P.I.

Findings from the data and the study will be disseminated through scientific presentations at national, regional or international conferences; or published in international scientific journals. Summaries may also be disseminated to the collaborators involved in the study.

## 7. STATISTICAL ANALYSIS PLAN

### 7.1 General analysis principles

#### 7.1.1 Participant population.

Patient-level outcome data will be used, and stratification and clustering will be taken into account in all analyses. The analysis population will consist of all enrolled participants who completed the baseline assessment. Missing follow-up measurements due to (1) death, (2) moving away from the study area, or (3) refusing to participate in the follow-up assessment will be accounted for in the analyses.

The analysis will use the intention-to-treat principle whereby all participant-level outcome data will be analyzed according to the arm to which the patient was allocated. Given the challenges of defining protocol violation in the context of a complex multi-component intervention like SINEMA, we will not perform per-protocol analyses but will instead summarize adherence to intervention components among intervention-arm participants and will summarize the frequency of visits to the village clinic in the control arm.

#### 7.1.2 Presentation and data handling rules.

Continuous variables will be reported as mean and standard deviation, if symmetric, or as median with 25th and 75th percentile, if not. Counts and proportions will be reported for categorical variables. Outliers will be identified through boxplots and histograms and will be queried at the data checking stage if an error is suspected. Ninety-five percent confidence

intervals will be presented, and significance of the primary outcome will be assessed based on a test at the two-sided 5% significance level.

## 7.2 Primary effectiveness analysis

The mixed effects framework will be used to model the primary outcome of short-term and long-term change in SBP with a random intercept for cluster (to account for the cluster randomized design) and fixed effects for township (to account for the stratified randomization procedure). More specifically, the primary outcome will be regressed on an indicator for treatment arm, baseline SBP, gender and age—in order to gain power—and indicator variables for township. Restricted maximum likelihood will be used together with the between–within method to calculate test degrees of freedom. Both methods have demonstrated good performance for binary outcomes and this good performance is expected for continuous outcomes, particularly when there are fewer than 40 clusters. For completeness, between-arm differences will also be presented based on the same model but with no adjustment for age and gender.

Baseline characteristics will be cross tabulated according to the randomized arm to visually check for appropriate balance and to provide an overview of the study population. If substantial baseline imbalance between the two arms is identified and the relevant variable is beyond the list of pre-specified variables for adjustment, additional sensitivity analyses adjusted for these imbalanced variables will be performed to ensure the robustness of the analysis.

## 7.3 Secondary effectiveness analyses

As indicated in **Table 4**, we plan to analyze both binary and continuous secondary outcome variables. Here we describe key elements of the analytical approaches and of any anticipated challenges to modelling these outcomes.

**Table 4. Definitions and Specifications of Outcome Variables**

| Outcome variables         | Definitions                                                                                                                                                                                                                                                                                                                                 | Specification for analysis |
|---------------------------|---------------------------------------------------------------------------------------------------------------------------------------------------------------------------------------------------------------------------------------------------------------------------------------------------------------------------------------------|----------------------------|
| Primary outcome    |                                                                                                                                                                                                                                                                                                                                             |                            |
| Systolic blood pressure   | Blood pressure is measured using a standardized electronic monitor (Omron HEM-7052) with individual in a seated position. Two reading are taken. If the differences between the two SBP readings is larger than 10mmHg, a third is taken. The mean of the only two SBP, or of the last two readings, will be used as the final measurement. | Continuous                 |
| Secondary outcomes |                                                                                                                                                                                                                                                                                                                                             |                            |
| Diastolic blood pressure  | As for SBP, the DBP outcome will be the mean of the only two, or of the last two readings of                                                                                                                                                                                                                                                | Continuous                 |

|                      |                                                                                                                                                                                                                                                                                                                                                                                                                                                                                                                                                                                                                                                                                                                                                                                               |                                                                                                        |
|----------------------|-----------------------------------------------------------------------------------------------------------------------------------------------------------------------------------------------------------------------------------------------------------------------------------------------------------------------------------------------------------------------------------------------------------------------------------------------------------------------------------------------------------------------------------------------------------------------------------------------------------------------------------------------------------------------------------------------------------------------------------------------------------------------------------------------|--------------------------------------------------------------------------------------------------------|
| Mobility             | 
DBP.
 
Mobility is measured using the “Timed Up and Go” test, a functional mobility test that requires the participants to stand up, walk 3 meters, turn, walk back and sit down. The mobility outcome will be specifically measured by the total time taken to complete the test, for which faster times (i.e. lower values) represent better functional mobility status. For participants who cannot complete the test (e.g. who cannot stand up), we will use a range of strategies (i.e. set to missing, set at maximum observed time or at some larger maximal tie) to deal with this issue and will evaluate how sensitive the estimated intervention effect is to those assumptions. The variable will also be dichotomized at a cut-off of 14s based on previous studies.
 | Continuous as total time to complete the test; and binary using cutoff of 14s                          |
| Physical activity    | 
Physical activity is measured with the short version of the International Physical Activity Questionnaire. Total physical activity score (MET-minutes/week) and activity classification (inactive, minimally active and health enhancing physical activity-HEPA) are derived according to the IPAQ scoring guideline.
                                                                                                                                                                                                                                                                                                                                                                                                                                                                  | Continuous as total physical activity score; and binary using cutoff of HEPA active vs. HEPA inactive. |
| Quality of life      | 
Quality of life is measured with EuroQol-5 Dimensions-5L (EQ5D), which consist of five dimensions and each with five levels of perceived problems. These dimensions are combined to give a five-digit code and a single index-based numerical value (ranged from 0 to 1) will be derived based on the value set for Chinese population.
                                                                                                                                                                                                                                                                                                                                                                                                                                                | Continuous as utility                                                                                  |
| Medication use       | 
Medication use is self-reported for each of three distinct medication types: anti-hypertensive medicine, aspirin and statin.
                                                                                                                                                                                                                                                                                                                                                                                                                                                                                                                                                                                                                                                           | Binary yes/no for each of three medication types.                                                      |
| Medication adherence | 
Self-reported medical adherence is measured by Morisky Green Levine Scale separately for anti-hypertensive medicine, aspirin and statins if the participant was taking the medicine. A score ranged from 0 to 4 are calculated by summing all coded answers where lower scores correspond to better medication adherence.
                                                                                                                                                                                                                                                                                                                                                                                                                                                              | The variable will be dichotomized as high adherence (0) vs. low to medium adherence (1-4).             |

---

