Patients' awareness and health behaviors also contribute to the suboptimal secondary prevention of stroke in rural China. With rapid urbanization, rural communities in China are left behind with large number of older people who are vulnerable. They have relatively poor health conditions and receive limited insurance protection through the China's New Cooperative Medical Scheme. Lacking awareness of the self-management of chronic conditions and economic difficulties result in poor adherence to secondary prevention. The PURE China study compared cardiovascular patients in urban and rural communities and found that the adherence to healthy lifestyles and the use of secondary prevention drugs are lower among cardiovascular patients in rural communities than in urban settings in all regions with different economic development levels. A study based on the China National Stroke Registry also showed that only 46.2% of the stroke patients continue the use of prescribed secondary prevention drugs after 3 months post hospital-discharge, and the persistence of use was positively associated with younger age, higher family income and the hospitals where the patients received treatment.

Mobile health (mHealth) technologies, in the form of text messaging and mobile applications, have emerged as a promising approach to support behavior change among both the providers and patients. Studies showed that mHealth technologies can empower patients' self-management of chronic conditions, increase access to healthcare services for vulnerable population, enhance communication flow, and improve the delivery of training to healthcare workers. However, despite the ubiquitous mobile network coverage and high penetration rate of mobile phones, few mHealth interventions have been implemented in rural China. The feasibility and effectiveness of such interventions is worthy of investigation.

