### 5.3 Sample size

Based on a sample of 1,250 prevalent stroke patients in 50 villages (with 25 villages per arm and on average 25 patients per village), assuming loss of 2 clusters (villages) per arm and loss of 1 patient per village on average, an intra-cluster correlation coefficient (ICC) of 0.04 (a conservative assumption), and a standard deviation (SD) for SBP pre-post change of 20 mmHg, the study has 83% power (with 2-sided alpha = 0.05) to detect a 5 mmHg net difference in pre-post change of SBP between intervention and usual care arms. Previous studies have been demonstrated that a 5mmHg difference is a meaningful change for stroke recurrence in 3-5 years. The effect size of a 5mmHg difference corresponds to a standardized effect size of 0.25 (5/20) and therefore we will have more than 80% power to detect such standardized effect sizes for secondary outcomes of interest, assuming the same level of clustering of those outcomes.

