### 1026 7.3.2 Secondary effectiveness analyses of binary outcomes

1027 Medication use, adherence, and physical activity levels are pre-specified binary outcomes. We  
1028 will analyze these variables using the generalized estimating equations (GEE) approach to  
1029 obtain population-averaged intervention effects. As with the primary analysis approach, strata  
1030 will be included as fixed effects in the model. In contrast to using random intercepts in the linear  
1031 mixed models used for the primary and continuous secondary outcomes, a working correlation  
1032 matrix will be used to account for clustering. More specifically, the modified Poisson GEE  
1033 approach (with log-link) will be used to obtain probability ratios (often referred to as risk ratios).  
1034 Although we expect to see correlation of outcomes within clusters, an independent working  
1035 correlation matrix will be used rather than exchangeable as it may provide greater stability with  
1036 the anticipated variability in cluster size. Robust standard errors will be used to account for  
1037 potential model misspecification. Importantly, because adherence can only be measured in

those who are taking medications, it will be important to determine the validity of a between-arm comparison. To this end, we will compare the predictors of medication use in each arm, for each of the three medications, thereby evaluating whether there is good internal validity of the comparison. In the case that we identify differences between arms in characteristics of those taking medications, we will adjust for such characteristics in the regression model.

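### The statement in section 5.3 of more than 80% power for secondary outcomes is not supported for medication adherence, which is analysed per drug, in takers only, and only as 0 versus 1-4.

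*Combined protocol and SAP*

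**What the plan says.** Section 5.3 starts from 1,250 patients in 50 villages, 25 per arm and 25 patients each. It proceeds "assuming loss of 2 clusters (villages) per arm and loss of 1 patient per village on average", with "an intra-cluster correlation coefficient (ICC) of 0.04 (a conservative assumption") and "a standard deviation (SD) for SBP pre-post change of 20 mmHg". From these it obtains 83% power for 5 mmHg. It converts 5/20 to a standardized effect of 0.25 and concludes: "we will have more than 80% power to detect such standardized effect sizes for secondary outcomes of interest". The only condition attached is that those outcomes cluster to the same degree as SBP.

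Table 4 derives a 0-4 adherence score, lower being better, separately for antihypertensives, aspirin and statins, in participants taking the drug. The analysis specification is: "The variable will be dichotomized as high adherence (0) vs. low to medium adherence (1-4"). No continuous or ordinal analysis is listed. In the same table, mobility and physical activity each have a continuous analysis beside the binary one.

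Section 7.3.2 on binary outcomes specifies a modified Poisson GEE. It recognises that adherence is measurable only in "those who are taking medications, it will be important to determine the validity of a between-arm comparison", and plans to compare predictors of medication use by arm and adjust if they differ.

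Section 4.3.3 names adherence as one of three targets of the finalized model. Section 5.7 describes the denominator differently from Table 4: the questions are put for drugs previously prescribed, not drugs being taken.

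**The concern.** The power sentence is carried over from an outcome that differs from adherence in two ways. SBP is continuous and measured in everyone. Adherence is cut to two levels and measured, drug by drug, in an unstated fraction of participants. Each difference can lower power, and section 5.3 allows for neither.

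The cut also hides change. Under 0 versus 1-4, a participant who improves from 4 to 1 counts as unchanged. For an outcome that the intervention is designed to move, a null result could be read against a stated power that was never worked out for it, and improvement short of a perfect score would not appear in the results.

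**Working it through.** **Inputs.** From section 5.3: 23 villages per arm and 24 patients per village after losses (25 − 2 and 25 − 1), ICC 0.04, standardized effect d = 0.25, two-sided alpha 0.05. The share f of participants taking a drug and the control proportion scoring 0, P(0), are not in the documents. Both are assumptions and are varied below.

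**Step 1: reproduce the plan's figure.** With m patients per village, the design effect is 1 + (m − 1) × ICC. At m = 24 it is 1 + 23 × 0.04 = 1.92. The effective number per arm is 23 × 24 / 1.92 = 552 / 1.92 = 287.5. The noncentrality is 0.25 / √(2/287.5) = 3.00. A noncentral t with 2 × 23 − 2 = 44 df gives 83.4%, matching the stated 83%.

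**Step 2: restrict to takers, still continuous.** Set m = 24f and change nothing else.

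| Takers f | m | Design effect | Effective n per arm | Noncentrality | Power |
|---|---|---|---|---|---|
| 100% | 24 | 1.92 | 287.5 | 3.00 | 83.4% |
| 75% | 18 | 1.68 | 246.4 | 2.78 | 77.5% |
| 50% | 12 | 1.44 | 191.7 | 2.45 | 66.8% |
| 25% | 6 | 1.20 | 115.0 | 1.90 | 45.8% |

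Power reaches 80% at f of about 84%.

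**Step 3: add the 0 versus 1-4 cut.** Treat 0.25 SD as a shift in an underlying normal score, so that the intervention proportion is p1 = Φ(Φ⁻¹(p0) + 0.25), where p0 = P(0). Apply ICC 0.04 to the binary outcome, which is how section 5.3 words its condition. The noncentrality is (p1 − p0) / √{[p0(1 − p0) + p1(1 − p1)] / effective n}, again on 44 df.

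Example with p0 = 0.50: p1 = 0.599. With everyone a taker the noncentrality is 2.39 and power is 64.7%. At 50% takers it is 1.95 and power is 48.0%.

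Over p0 from 0.20 to 0.70:

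- everyone a taker: 57-65%
- 75% takers: 50-58%
- 50% takers: 41-48%
- 25% takers: 27-32%

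If ICC 0.04 is placed on the underlying score instead, simulation gives 69-74% with everyone a taker (P(0) 0.30-0.70), still below 80%.

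**Step 4: conditions under which the statement survives.** Read 0.25 as a binary-scale effect (Cohen's h, for example 50% versus 62.4%). Power is then about 84% with everyone a taker, 78% at 75% takers and 67% at 50%. With an assumed ICC of 0.01, a continuous measure has 90% at 75% takers, and the Step 3 split at p0 = 0.50 has 83% with everyone a taker.

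**Step 5: information lost by the cut alone.** Under proportional odds, 0 versus 1-4 keeps about 50%, 67%, 87% and 96% of the information in the five-level score when P(0) is 0.20, 0.30, 0.50 and 0.70, in four assumed distributions. The loss is large when few takers score 0 and small when most do.

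**The case against.** The strongest reply is that section 5.3 is conditional: it speaks of an effect of 0.25 and of equal clustering, and Step 4 shows readings under which more than 80% holds. That stands. A reader might infer from Steps 2 and 3 that adherence cannot have 80% power. The documents do not support that, because they give no taker share, no expected adherence and no ICC for this outcome.

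A reader might also take the background statement that "only 46.2% of the stroke patients continue the use of prescribed secondary prevention drugs" as this trial's taker share. It is a registry figure for persistence on prescribed drugs three months after discharge, so no conclusion here rests on it.

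The planning losses may be pessimistic too. Part B section 3.1 reports 1,266 participants assessed at 12 months, about 25 per village (1,266 / 50). With 25 villages of 25 per arm, a continuous measure has 87% power in everyone and needs about 69% takers for 80%. This eases the shortfall but does not make the statement applicable to a subset of unknown size.

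Finally, the cut is pre-specified and its risk ratio is easy to interpret. Formal significance is set only for the primary outcome (section 7.1.2), so a null adherence result need not be over-read. These points stand against replacing the pre-specified analysis. They do not justify the power sentence. The section 7.3.2 safeguard for takers addresses comparability of the arms, not power or lost information.

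**Conclusion.** The power statement is not supported for medication adherence as the plan analyses it. With the plan's own inputs it already fails for a continuous measure once fewer than about 84% take the drug. If 0.25 SD refers to the underlying score and the binary outcome has ICC 0.04, it fails for the 0 versus 1-4 split even with everyone a taker (about 57-65%).

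The two causes are separate. The taker restriction would remain under any analysis of the score, and it is often the larger one. The cut adds a loss that may be substantial or slight, depending on the score distribution.

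A reader might conclude that an ordinal model should become the main adherence test. The documents do not support that: the model would not cure the taker restriction, its gain varies, and it would displace a pre-specified and interpretable contrast. The case is for correcting section 5.3 and adding a supportive analysis.

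**What to change.** 1. **Section 5.3.** Limit the sentence on more than 80% power to secondary outcomes analysed as continuous in all participants. For adherence, state power or the detectable difference per drug over a stated range of taker shares. For example, with control P(0) of 50% and ICC 0.04, the smallest difference with 80% power is 11.8 percentage points with everyone a taker, 12.7 at 75%, 14.3 at 50% and 18.2 at 25%.

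2. **Table 4 and section 7.3.2.** Keep the 0 versus 1-4 risk ratio. Add a supportive ordinal or mean-score analysis of the 0-4 score per drug, with township as a fixed effect and village clustering, so that change within 1-4 is visible.

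3. **Denominator.** Reconcile section 5.7 (previously prescribed) with Table 4 (taking), since it determines the number analysed.

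**Cost.** No new data, one extra model per drug, and a less favourable stated power for adherence. A mean-score difference or common odds ratio is less intuitive than a risk ratio, which is a further reason to keep it supportive. Part B is dated August 2022, after the July 2018 assessment, and keeps its non-mortality analyses in line with the one-year plan. Any score analysis added now should be labelled as a later addition, beside the unchanged pre-specified result.
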